Clinic-based rehabilitation (face-to-face sessions)									
Knee Care at Home (face-to-face and remote sessions)									
Outcome measures									
Patient-reported									
Pain	x	x	x	x	x	x	x	x	x
Pain catastrophising	x	x	x	x	x	x	x	x	x
Symptoms	x	x	x	x	x	x	x	x	x
Function	x	x	x	x	x	x	x	x	x
Quality of life	x	x	x	x	x	x	x	x	x
Anxiety/depression/stress	x	x	x	x	x	x	x	x	x
Clinician-reported									
Height	x	x	x	x	x	x	x	x	x
Mass (weight)	x	x	x	x	x	x	x	x	x
Joint effusion		x	x	x	x	x	x	x	x
Range of motion		x	x	x	x	x	x	x	x
Muscle length		x	x	x	x	x	x	x	x
Muscle strength		x	x	x	x	x	x	x	x
Physical functional performance									
Hop distance (single leg)						x	x	x	x
Stair (ascent/descent)		x*	x*	x*	x	x	x	x	x
Clinical relevance									
Symptom state		x	x	x	x	x	x	x	x
Clinical benefit		x	x	x	x	x	x	x	x
Clinical difference		x	x	x	x	x	x	x	x

### Data management

The orthopaedist and lead investigator will oversee data collection, development and security. Complete data analysis will be conducted after the trial protocol. The orthopaedist will manage access to clinical records stored in HME’s secure database and only disclose the study’s relevant information. Any necessary pictures will be encrypted for protection and promptly deleted after the trial concludes. All participant data will be linked to a logged patient number inputted into the analysis software along with other relevant data, and all spreadsheets will be encrypted.

The Limb Symmetry Index will calculate the range of motion, muscle length, muscle strength and hop performance by comparing the involved and uninvolved sides and normalising for mass and height.^4^ Additionally, physical functional performance testing will be supplemented with data from the CR10 scale and VAS for pain.

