Knee joint effusion	Patellar Tap/Ballottement Test^26^	Patients are evaluated for knee effusion while lying supine on an examination table. The assessor applies downward strokes from the thigh to the leg with the non-dominant hand and then grasps the upper portion of the knee just above the patella. Using two fingers of the dominant hand, they press the patella against the femur in a posterior direction. Increased patellar waving or a spongy joint sensation indicates a positive test result for knee effusion. The test is then repeated on the opposite knee for comparison.
Passive knee flexion and extension range of motion	Hand-held Goniometry (HHG)^27^	Passive knee extension and flexion range of motion are measured in patients using a long-arm goniometer. Both knees are measured for comparison with the goniometer axis placed at the lateral epicondyle of the femur. The proximal arm of the goniometer is placed alongside the lateral midline of the femur, using the greater trochanter as a reference. In contrast, the distal arm is placed alongside the lateral midline of the fibula, using the lateral malleolus and fibular head as references. For passive knee flexion, the patient lies supine on the examination table, with the lower limbs in an anatomical position. The assessor flexes the patient’s knee through the available range of motion by sliding the patient’s foot along the table towards the pelvis and then taking the passive range of motion measurement. For passive knee extension, the patient lies in a supine position on the examination table with the lower limbs in an anatomical position and a towel under the ankle with the knee extended as far as possible. The assessor provides added pressure to the knee in the direction of extension and then takes the passive range of motion measurement.

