Knee extensor and flexor muscle length	HHG^27^	The length of the knee flexors and knee extensors muscles in patients is measured using specific tests and a long-arm goniometer. The measurements are taken on both knees for comparison, with the goniometer axis placed at the lateral epicondyle of the femur. For the knee flexors muscle length (Thomas test), the patient lies in a supine position with the hip of the lower extremity to be measured and extended on the examination table. The leg is supported on the table, and the knee is just past the table’s edge (test side). The patient is asked to flex the contralateral hip and grasp the knee to the chest until the lumbar spine is felt to flatten against the table, and the measurement of knee flexion is taken (test side). For the knee flexors muscle length (prone technique), the patient lies in a prone position with both hips of the lower extremity extended on the examination table. The knee to be tested moves to maximal achieved flexion, and the measurement of knee flexion is taken (test side). For the knee extensors muscle length (distal hamstring length test), the patient lies in a supine position with the hip of the lower extremity to be measured in 90 degrees of flexion on the examination table. While the assessor helps maintain the hip position, the patient executes a knee extension, and the knee flexion is measured (test side).
Extensor and flexor isometric muscle strength	Hand-held Dynamometry^28^	The microFET2 is used to measure the isometric strength of the hamstrings and quadriceps in patients. This measurement is taken on both knees to allow for comparison. The patient is seated on an examination table with their hips and knees flexed at a 90-degree angle. The assessor stabilises the patient’s leg using the leg of the examination table as support for the hand-held dynamometer. The patient is then instructed to apply maximum force against the device. First, the patient is asked to try to extend the knee, and then they are asked to flex the knee. Three repetitions are performed for both extension and flexion.

**Table 4 T4:** Physical functional performance and clinical relevance outcome measures

Outcome	Assessment tool	Procedures
Physical functional performance		

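### A single Limb Symmetry Index rule covers angles as well as force and distance; as a ratio it breaks down for passive knee extension, and Table 3 reverses the muscle-length labels

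*Protocol article*

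**What the plan says.** Data management sets one derivation for four outcomes: "The Limb Symmetry Index will calculate the range of motion, muscle length, muscle strength and hop performance by comparing the involved and uninvolved sides". The sentence goes on "and normalising for mass and height". It cites a reference but gives no formula, and it does not separate angles from force or distance.

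Table 3 (Outcomes measures and assessments) describes the measurements. Passive flexion and extension are read with a long-arm goniometer: "Both knees are measured for comparison with the goniometer axis placed at the lateral epicondyle of the femur". Extension is taken with "a towel under the ankle with the knee extended as far as possible". No zero convention is given. Strength is an isometric force on both sides. Table 4 gives hop as a distance for both limbs.

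The muscle-length row of Table 3 names three tests:
- "For the knee flexors muscle length (Thomas test), the patient lies in a supine position"; the reading is knee flexion with the hip extended.
- "For the knee flexors muscle length (prone technique), the patient lies in a prone position"; the reading is maximal knee flexion.
- "For the knee extensors muscle length (distal hamstring length test"; the patient straightens the knee with the hip at 90 degrees, and the remaining knee flexion is read.

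Table 5 schedules range of motion and muscle length at all eight visits from week 2 to week 36. Statistical analysis plans baseline-adjusted linear mixed models with a group-by-time interaction.

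**The concern.** A ratio of sides suits quantities that are positive and well away from zero, such as force and hop distance. Passive extension of a sound knee is a different kind of number. If full extension is recorded as 0 degrees, the denominator sits at or around zero and may be negative in a knee that hyperextends. The distal hamstring angle can also approach zero in a flexible patient. In both cases a larger reading means a worse limb, so the index would point the opposite way from strength and hop.

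If such values were entered in the planned mixed models, undefined ones would drop out and a few extreme ones could dominate the fit. The same difficulty would recur at every visit.

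Two further points lie beside this one. Both limbs share one body mass and one height, so correcting both sides for them cannot alter a ratio. And the muscle-length labels in Table 3 conflict with the tests they describe, so a muscle-length result could be credited to the wrong muscle group.

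**Working it through.** The plan gives no figure to reproduce. The check is arithmetic on illustrative values, which are assumptions throughout.

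**Assumed definitions.** Index = 100 x involved / uninvolved. Difference = involved - uninvolved. Full extension = 0 degrees, with positive values for a deficit and negative values for hyperextension.

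**1. Passive extension.**

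| Involved (deg) | Uninvolved (deg) | Index | Difference (deg) |
|---|---|---|---|
| 5 | 0 | undefined | 5 |
| 5 | 1 | 500% | 4 |
| 5 | 2 | 250% | 3 |
| 5 | -2 | -250% | 7 |
| 0 | 0 | undefined | 0 |

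The differences range from 0 to 7 degrees and are always defined. The index changes sign, jumps by hundreds of percentage points for a change of a degree or two in the healthy knee, and has no value for a patient who is perfectly symmetric at full extension.

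**2. How often the denominator fails.** The article gives no distribution for the uninvolved knee. Assuming normal readings with mean -3, 0 or 3 degrees and SD 2 or 4, recorded to the nearest degree, simulation puts the denominator at exactly 0 in about 6% to 20% of readings and below 0 in about 4% to 90%. With recording to the nearest 5 degrees, exact zeros rise to about 37% to 79%. The ranges are wide because the inputs are assumed, but zeros are not rare in any of these cases.

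**3. Dependence on the zero convention.** If a straight knee is recorded as 180 degrees, the first, second and fourth pairs become 175/180 = 97.2%, 175/179 = 97.8% and 175/182 = 96.2%. The ratio is then stable and larger is better. The same knees therefore give either a usable number or none, depending on a convention that the article does not state.

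**4. Angles that are not exposed.** Flexion range has a denominator far from zero: 110/135 = 81.5% and 125/140 = 89.3%. No near-zero problem has been shown for the Thomas and prone tests, which read knee flexion angles.

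**5. Mass and height.** For one person with mass m and height h, (F1/(m x h)) / (F2/(m x h)) = F1/F2. With forces of 210 and 300, the index is 70.0% at 60 kg and 1.60 m, at 80 kg and 1.75 m, and at 100 kg and 1.90 m. Normalisation does change a non-ratio quantity: the difference of 90 becomes 0.94, 0.64 and 0.47 after division by m x h.

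**6. Labels.** The hamstrings flex the knee, so a distal hamstring length test measures a knee flexor; Table 3 files it under extensors. Bending the knee with the hip extended, as in the Thomas and prone tests described, stretches the knee extensors; Table 3 files both under flexors. All three labels are reversed. This step needs no assumption about the formula or the goniometer zero.

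**The case against.** The strongest reply is that the formula and the zero are both assumed here. The article cites a source for the index, a full protocol could define both, and a journal article commonly leaves such detail to that document. With a straight knee at 180 degrees the instability disappears. This stands as a limit: the extension result is conditional. It does not remove the point, because the article does not merely omit a formula. It states that one index applies to range of motion and muscle length alike, and for two of those angles whether it works depends on an unstated choice.

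A second reply is that "comparing the involved and uninvolved sides and normalising for mass and height" can be read as two steps, a side comparison and a separate normalisation of per-limb values. That reading is possible, and under it the normalisation would have an effect. Under the ratio reading it changes no result, so it is redundancy rather than bias.

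Third, Statistical analysis does not say that the index, rather than the angle in degrees, enters the mixed models. That is correct, so the consequence for the models is conditional too.

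Fourth, the label error leaves the recorded angles unchanged, and each test is named and described, so a careful reader can identify the muscle. That stands; the risk is in reporting.

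A reader might go further and infer that all these outcomes would be wrong, or that a main clinician-reported result is lost. The documents do not support either. Strength, hop, flexion range and the Thomas and prone angles remain computable, and Table 3 lists its measures without ranking them.

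**Conclusion.** The concern holds in a limited form. Under the usual ratio and a zero at full extension, both assumed, the index is unusable for passive knee extension and can be for the distal hamstring angle, and for both it runs in the opposite direction to strength and hop. For an involved knee at 5 degrees, moving the healthy knee among 0, 1 and -2 degrees takes the index from undefined to 500% to -250%, against differences of 5, 4 and 7 degrees. Under a 180-degree convention the ratio is stable but depends on that choice.

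The mass and height normalisation is redundant in a ratio and does no harm to the strength and hop indices. The reversed labels in Table 3 are an error whatever the formula, confined to how results are named and interpreted.

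Sample size calculation rests on KOOS pain, which none of this touches.

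**What to change.** 1. In Data management, restrict the index to strength and hop and state its formula.
2. Analyse passive extension and distal hamstring length as the side-to-side difference in degrees, stating the goniometer zero and the sign. The other angles may use the same scale for consistency, though their ratios are computable.
3. Remove mass and height from the index. Apply that normalisation only to per-limb strength or hop values, if these are analysed.
4. In Table 3, put the distal hamstring test under knee flexors and the Thomas and prone tests under knee extensors.

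The cost is wording and derivation code. Both limbs are already measured, so no assessment, visit or sample size changes.

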### Statistical analysis

The strength of evidence for the applied methods will be measured using a significance level of 5%. The analysis will adhere to intention-to-treat principles, and patient characteristics will be presented using descriptive statistical tests. The chosen method for examining outcomes will account for within-subject correlations in repeated measures analysis of variance.^20^ To assess the effect of treatment, between-group differences will be calculated by constructing linear mixed models with interaction terms of treatment groups versus time. All models will be adjusted for baseline estimates.

The Minimal Clinically Important Difference (MCID) will be determined using an anchor-based or distribution-based method if the former is unsuitable. The anchor-based technique will use the receiver operating characteristic (ROC) curve to identify the optimal cut-off point for distinguishing between groups with minimal and no change. The cut-off value will be determined by maximising specificity and sensitivity. The area under the ROC curve will be used to assess reliability, with acceptable values falling between 0.70 and 0.80 and excellent values ranging from 0.80 to 0.90. The distribution-based method will rely on SD and effect size-based estimation. Across various studies, an MCID corresponds to an SD value of 0.5, and to calculate the change MCID, the SD of the baseline scores is multiplied by 0.2 (small effect size).^21^

All statistical analysis and presentation will adhere to the recommendations outlined in CHecklist for statistical Assessment of Medical Papers: the CHAMP.^20^

### Benefits and harms

While benefits from the trial are not guaranteed, significant adverse effects are not expected. Participants may experience increased discomfort after exercising, a common side effect when starting a new activity. The KC@H programme is insured to provide coverage for participants in the event of any damage.

The KC@H programme carries a potential risk of adverse events, which will be minimised through precautionary measures. Participants are encouraged to contact the lead investigator using the provided phone number for guidance or in case of any adverse events or questions. All adverse effects will be documented and reported to the Institutional Review Boards of the Universidade de Évora and the HME.

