## Abstract

Patients who cannot fully comply with conventional clinic-based rehabilitation (CR) sessions after ACL reconstruction (ACLR) may find additional internet-based sessions beneficial. These remote sessions include therapeutic exercises that can be done at home, potentially extending the reach of rehabilitation services to underserved areas, prolonging the duration of care and providing improved supervision. The study’s main purpose is to determine if the Knee Care at Home (KC@H) programme is more effective than conventional CR alone in improving patient-reported, clinician-reported and physical functional performance outcome measures after ACLR. Additionally, the trial assesses the significance of changes in outcome measures for clinical practice.

This protocol outlines a randomised controlled trial for postoperative recovery following ACLR. Adult participants of both sexes who meet specific criteria will be randomly assigned to either the CR group or the KC@H group. Only the latter group will receive internet-based sessions of therapeutic exercises at home and CR sessions. A follow-up evaluation will be conducted for both groups 12 weeks after the intervention ends.

The trial protocol was approved by the Ethics Committee of the Universidade de Évora and complies with the Code of Ethics of the World Medical Association. All recordings will be stored on a secure server with limited access and deleted as soon as they are no longer needed.

The KC@H programme is expected to be superior to conventional CR for patients recovering from ACLR across multiple outcome measures. Also, the programme has the potential to promote superior recovery and extend the reach and duration of care.

Trial registration number: NCT05828355.

WHAT IS ALREADY KNOWN ON THIS TOPICCommunication technologies are being used for home-based rehabilitation after ACL reconstruction (ACLR). More data are needed to confirm their effectiveness compared with face-to-face rehabilitation.WHAT THIS STUDY ADDSBy demonstrating the effectiveness of the Knee Care at Home (KC@H) programme in maximising the recovery of patients after ACLR, we can offer healthcare professionals an innovative and complemental approach.HOW THIS STUDY MIGHT AFFECT RESEARCH, PRACTICE OR POLICYThe KC@H programme has the potential to expand the reach of rehabilitation services to underserved areas, prolong the duration of care and improve supervision using existing communication technologies.

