### Intervention

The intervention begins immediately after the first postoperative consultation. Participants in both groups are advised to attend individual face-to-face sessions with a physiotherapist at a rehabilitation clinic and any postoperative consultation with the orthopaedist. We acknowledge that there may be accessibility issues in face-to-face sessions^7 9^ and variations in content and exposure^4^ that could impact our results. We randomly assigned both groups under comparable circumstances in our trial protocol to account for this. While we cannot control face-to-face sessions, we will monitor attendance and coverage weekly for both groups using a short messaging service. Additionally, we will strive to monitor the content similarity between face-to-face and remote sessions.

The intervention consists of internet-based synchronous remote sessions using videoconferencing software and face-to-face sessions. This enables participants to engage in therapeutic exercises at home under the guidance of an exercise and health coach. The remote sessions take place over 22 weeks, 3 days a week, lasting 40 min.

To provide a comprehensive description of the intervention, we have developed table 1 under the Template for Intervention Description and Replication recommendations.^18^

**Table 1 T1:** Intervention description

Item	Comparison arm	Intervention arm
Brief name	Clinic-based rehabilitation	KC@H programme
Where	Rehabilitation clinic	Rehabilitation clinic and patient home
How	Face-to-face sessions	Face-to-face and remote sessions
Who	Physiotherapist	Physiotherapist and exercise and health coach
What	Dependent on rehabilitation clinic protocol and physiotherapist judgement	(face-to-face sessions) Dependent on rehabilitation clinic protocol and physiotherapist judgement. (remote sessions) KC@H manual providing general information, therapeutic exercises, time-based standards and criterion-based standards for progression
When	Starting from the second week after ACLR	Starting from the second week after ACLR

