How much	Expected to last for 22 weeks, the number of sessions will be dependent on the patient’s preference and the availability of the rehabilitation clinic	(face-to-face sessions) Expected to last for 22 weeks, the number of sessions will depend on the patient’s preference and the availability of the rehabilitation clinic. (remote sessions) The programme will last for 22 weeks, with three sessions per week, each lasting 40 min. The exercise load will be monitored using the CR10 scale, while the pain intensity will be assessed using the VAS at the beginning and end of each session.
Tailoring/modifications	None	Time-based standards: immediate stage (0–2 weeks); early stage (2–4 weeks); intermediate stage (4–12 weeks); late stage (12–16 weeks); final stage (16–24 weeks) Criterion-based standards: inflammatory response; range of motion; lower limb muscle strength; gait; balance; core stability; agility; plyometrics

ACLR, ACL reconstruction; CR10, Borg Category Ratio Scale; KC@H, Knee Care at Home; VAS, Visual Analogue Scale.

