#### KC@H programme manual

The KC@H manual describes all therapeutic exercises included in the programme, with patient progression determined based on objective criteria rather than a predetermined recovery timeline after ACLR.^19^ This approach, which combines time- and criterion-based standards, helps prevent adverse events during remote sessions and allows the intervention to be applied in various clinical scenarios.^19^

Due to the unavailability of specialised strength equipment for our remote sessions, we have used the CR10 scale to monitor training load and progress. For every exercise, we will record the duration (in minutes), number of sets and repetitions and the level of completion (complete, incomplete, unable to perform). Additionally, we will document the pain intensity at the start and end of each remote session. The orthopaedist will receive a detailed progress report containing all the information gathered during the remote sessions.

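### The only stated adverse-event route is a phone call from the participant, so capture can differ between an arm with up to 66 coached sessions and an arm with none

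*Protocol article*

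**What the plan says.** All references are to the protocol article.

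- **Reporting route (Benefits and harms).** "Participants are encouraged to contact the lead investigator using the provided phone number for guidance or in case of any adverse events or questions". The next sentence adds: "All adverse effects will be documented and reported to the Institutional Review Boards of the Universidade de Évora and the HME". The same section accepts that the programme has a potential risk of adverse events.
- **Who has remote sessions (Abstract).** "Only the latter group will receive internet-based sessions of therapeutic exercises at home and CR sessions".
- **How many (Intervention and Table 1).** "The remote sessions take place over 22 weeks, 3 days a week, lasting 40 min".
- **What is recorded in them (KC@H programme manual).** The coach notes duration, sets, repetitions and level of completion for every exercise. "Additionally, we will document the pain intensity at the start and end of each remote session". This is then passed on: "The orthopaedist will receive a detailed progress report containing all the information gathered during the remote sessions".
- **What both arms share.** The orthopaedist's consultations and the assessor's evaluations take place at t0 to t6 and f1 in both arms (Postoperative phases; Table 5). For face-to-face physiotherapy, "we will monitor attendance and coverage weekly for both groups using a short messaging service".
- **Who knows the allocation (Blinding).** Participants, orthopaedists and coaches know it. Only the outcome assessor is blinded.

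**The concern.** A route that depends on the participant choosing to phone records only what the participant thinks worth a call. That threshold may shift when someone is seen by a coach three times a week, asked about pain twice a session, and followed through progress reports to a trial clinician. A KC@H participant with a problem has a regular, documented occasion on which it can come to light. A CR participant with the same problem attends a rehabilitation clinic whose sessions the protocol says it cannot control, and must either phone or wait for the next consultation.

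What is at stake is the reading of the safety record. The protocol attaches a potential risk to the programme and says its progression standards help to prevent adverse events during remote sessions. Event counts by arm will bear on both statements. If KC@H shows more events, three explanations compete: more observation, more exercise, or chance. If CR shows few, some of its events may simply not have been recorded.

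**Working it through.** **1. Planned remote sessions.** The intervention runs from week 2 to week 24: 24 - 2 = 22 weeks, which agrees with Table 1 ("The programme will last for 22 weeks, with three sessions per week, each lasting 40 min"). Sessions: 22 x 3 = 66. Time: 66 x 40 min = 2,640 min = 44 hours. The article does not print the total of 66; it follows from the schedule and is a maximum, reached only with full attendance.

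**2. Planned trial contacts per participant after t0, within the intervention period.**

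| Contact | CR | KC@H |
|---|---|---|
| Consultations t1 to t6 | 6 | 6 |
| Remote sessions | 0 | 66 |
| Subtotal | 6 | 72 |
| Weekly messages (one per week, 22 weeks) | 22 | 22 |
| Total | 28 | 94 |

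The ratio is 72 / 6 = 12 without the messages and 94 / 28 = 3.4 with them. Clinic physiotherapy is left out because its amount is not fixed in either arm. The follow-up consultation f1 adds one contact to each arm.

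**3. Which contacts are said to ask about adverse events?** None. The weekly message is described as covering attendance and coverage. Table 5 lists pain and joint effusion at the shared evaluations but has no adverse-event row. The coach's records are pain, exertion and exercise completion.

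**4. What unequal capture would do.** The documents give neither event risks nor capture rates, so every such value here is an assumption. Let the true risk r be the same in both arms, with capture probability c0 in CR and c1 in KC@H. The expected number of participants with a recorded event is 28 x r x c, using the planned 28 per group. The observed ratio is c1 / c0, whatever r is. With r = 20%:

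| Capture, CR | Capture, KC@H | Recorded, CR | Recorded, KC@H | Ratio |
|---|---|---|---|---|
| 0.95 | 0.95 | 5.3 | 5.3 | 1.0 |
| 0.7 | 0.8 | 3.9 | 4.5 | 1.14 |
| 0.7 | 0.9 | 3.9 | 5.0 | 1.29 |
| 0.5 | 0.9 | 2.8 | 5.0 | 1.8 |
| 0.3 | 0.9 | 1.7 | 5.0 | 3.0 |

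For example, 28 x 0.20 x 0.9 = 5.04 and 28 x 0.20 x 0.5 = 2.8, and 0.9 / 0.5 = 1.8. In absolute terms the gap runs from less than one participant to about three.

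**5. With a common enquiry.** If both arms are asked the same question on the same occasions and capture is thereby equal, equal true risks give equal expected counts, as in the first row.

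**The case against.** The strongest reply is that this is an omission and not a stated rule. The phone number serves for guidance and questions as well as events, so it reads as a help line. The article does not say that events are captured only by phone, and its promise to document all adverse effects sets no limit on route. Visit questions and event forms are commonly left to a full protocol, which is not shown. This carries weight, and it is why the point is an improvement to make and not a demonstrated failure. It does not remove the point: the article does name a route, that route is passive, and it sits in a design with very unequal contact.

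Four further limits stand.

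- A reader might infer that event counts will differ, and through ascertainment alone. The documents do not support this. The phone line is open equally to both arms, coaches are not said to log adverse events, and up to 44 hours of added exercise could cause a real difference.
- A reader might also set 66 contacts against none. That is true of coach sessions only; the shared consultations and weekly messages reduce the imbalance.
- Adverse events are not an outcome in Tables 2 to 5, and Statistical analysis states no between-arm safety comparison. No planned test is biased.
- The ratios in the working rest on assumed capture rates. Near-equal capture gives a ratio close to 1.

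**Conclusion.** The point holds in a limited form. As written, the plan allows adverse events to be captured unequally by arm, with under-recording in CR the main risk, and any difference in counts could not be attributed to a cause. This rests on three readings of the article: the phone call is the only route it names, only KC@H has the coach sessions and the reports that flow from them, and no shared contact is described as asking about adverse events. If a fuller protocol already holds a common scheduled enquiry, the point falls away.

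The size is unknown. Under the assumptions shown, the spurious ratio runs from 1.0 with equal capture to 1.8 at 90% against 50%, and to 3.0 at 90% against 30%. The consequence is confined to safety reporting; the efficacy analysis is untouched. The change is still worth making, because it is cheap and events missed in CR cannot be reliably recovered afterwards.

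**What to change.** - Add one fixed adverse-event question, identical in both arms, to the weekly message already sent.
- Have the orthopaedist ask the same scripted question at each consultation t1 to t6 and f1 in both arms. The blinded assessor should not ask it, since the answer could reveal the allocation.
- Keep the phone line. Report events by arm from all three routes open to both arms: message, consultation and phone. Leaving out phoned-in events would lose real events for no gain in symmetry.
- List events first detected in remote sessions separately for KC@H, labelled as having no counterpart in CR.

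The cost is one question in an existing message and one on the visit form, slightly more reporting work, and higher recorded event counts in both arms, which the report should explain. Symmetric enquiry deals with contact frequency only in part: coaching may still make KC@H participants readier to report, and the extra exercise exposure remains part of the treatment difference. The report should say so.
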